| Research procedure | 
(1) Screening for inclusion (D-14) : After the subjects signed the informed consent, all pre-enrollment screening examinations were conducted in the periodontal/emergency comprehensive clinic of the research institution. Subjects who met the inclusion criteria and did not meet the exclusion criteria were selected Join the group. The investigator selected the subject's proposed treatment site (single tooth position/subject).
 
(2)Periodontal primary treatment (D-14~D1) : Periodontal primary treatment includes supragingival scaling, subgingival scaling and root treatment The surface is flat. Divided into 3 times, the specific treatment steps are as follows:
 
 
■ Supragingival cleaning (D- 14) : normal saline rinse and gargle, whole mouth ultrasonic supragingival cleaning and polishing, normal saline rinse;
 
■ Subgingival scaling (D-7±1, non-therapeutic dental area) : 2% bilan anesthesia, half-mouth ultrasonic subgingival scaling, flat root surface, polishing, normal saline rinse;
 
■ Subgingival scaling (D1, including treatment area) : 2% bilan anesthesia, the other half of the mouth ultrasound subgingival scaling, root surface flat, polishing, normal saline rinse.
 
 
(3) Local injection therapy (D1) : According to the randomly assigned number, all subjects were given bilateral multi-point local injection therapy of hDP-MSC cells/normal saline immediately after the peridental foundation treatment was completed. The local injection method for the peridental defect site is: Under local anesthesia, the periodontal probe was used to determine the top position of the alveolar ridge, and the needle was injected into the bottom of the periodontal bag (in the surrounding tissue at the bottom of the periodontal bag). After the needle reached the medial periodontal membrane of the alveolar ridge and touched the junction between the bone surface and the tooth root, the multi-point interstitial injection was performed on both sides of the buccal (lip) and lingual and palatine sides with a 1ml spiral syringe. The injection time is 20-30 seconds at each point. The stop point of the injection needle is located on the tooth root surface to ensure that the injected stem cell preparation can be in the tooth root The area is clustered. Specific operations are as follows:
 
 
■ DPSCs injection group: 48 subjects. Immediately after the completion of periodontal basic treatment, the patient was given bilateral multi-point injection at a single dental position, and the therapeutic dose was <math>1 \times 10^7</math> hDP-MSC cells (0.6mL suspension of normal saline)/dental position/person.
 
■ Saline iniecton group: 48 subjects. Immediately after the completion of periodontal basic treatment, the patient was given bilateral multi-point injection at a single dental position, and the therapeutic dose was 0.6mL normal saline/dental position/person.
 
 
Local stem cell secondary injection therapy (D30±3) : Only for secondary stem cells in the second phase of this study Subjects in the administration group. At the end of a one-month follow-up, the subjects were given more hDP-MSC cells on both sides Point local injection therapy. The local injection method of periodontal defect site is the same as the first local injection treatment:
 
 
■ Double DPSCs iniecton group: After 1 month follow-up, the subjects received bilateral multi-point injection at a single dental position and the therapeutic dose It was <math>1 \times 10^7</math> HDP-MSC cells (saline 0.6mL suspension)/dental position/person.
 
 
(4) Observation (D1) : After treatment, all subjects were admitted to the periodontal/emergency comprehensive clinic 2 Hours of adverse reactions observation and safety assessment.
 
(5) Follow-up (D7±1 telephone follow-up, D30±3, D90±3, D180±5, D360±5) :
 
 
■ Post-treatment follow-up: Subjects were followed up at D7±1 (telephone follow-up), D30±3, D90±3, and D180±5 once each after discharge, and clinical safety and efficacy indexes were collected.
 
■ Long-term follow-up: After the end of treatment, D360±5 follow-up was conducted once, clinical efficacy and immunological evaluation indicators were collected, and the study was ended.
 
 |

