| Effectiveness evaluation | 
① Primary efficacy measures
 
 
■ Oral clinical testing indicators: at screening periods, pre-treatment periods, and follow-up periods D90±3, D180±5, D360±5, examination was performed using a Florida probe, and the measurement of D90±3 was used as the evaluation endpoint.
 
■ attachment level AL (Periodontal depth PD + gingival recession GR).
 
 
② Secondary efficacy indicators
 
 
■ Imaging test indicators: at screening periods and follow-up periods D90±3, D180±5, and D360±5, examinations was performed using a Florida probe, and the screening periods was used as baseline, D180±5 measured value was used as the evaluation endpoint.
 
• Changes in periodontal defect height at 3, 6, and 12 months after the end of treatment compared with baseline (CBCT measurements, change of periodontal defect height = difference in distance from the cemento-enamel to the top of the alveolar ridge).
 
• Changes in mean alveolar ridge density at 3, 6, and 12 months after the end of treatment compared to baseline (CBCT measurements).
 
■ Oral clinical testing index: at screening periods and follow-up periods D90±3, D180±5, D360±5, using Florida probe for examination, use the measurement of D90±3 as the evaluation endpoint.
 
• PD compared to baseline;
 
• Periodontal healing compared to baseline (probing bleeding index BOP, gingival recession GR, tooth mobility TM).
 
 |

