##### **3. Imaging examination**

3-12 months after hDP-MSC localized injection treatment, compared with pre-treatment and basic periodontal treatment only, oral CBCT examination can see the hard tissue proliferation in the periodontal area of the injected teeth and the alveolar bone edge, or the volume of the periodontal hard tissue defect reduced.

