#### **(V) Study design**

**1. This study is a single-center, randomized, controlled study of basic periodontal basic treatment combined with hDP-MSC localized injection, the sample size was 96 cases.**

**2. The study conducted two phases: the first phase consisted two groups randomized according to a 1:1 ratio; the second phase consisted of three groups randomized according to a 1:1:3 ratio.**

**2.1 Randomization method:** The randomization method for each stage of the study was district group randomization, and the statistician used SAS 9.4 software to generate random group codes. In phase 1, subjects were assigned to the DPSCs injection group and saline injection group, randomization envelopes were retrieved by the SAS unit upon completion of this phase; Phase II subjects were assigned to the single DPSCs injection group, double DPSCs injection group and the saline injection control group in the ratio of 1:1:3 according to the code of this phase.

**2.2 Inclusion Criteria:** Subjects must meet all of the following criteria to be included:

- (1) Age 18-65 years old, gender is not limited;
- (2) Voluntarily participate in this clinical study and sign the informed consent form;
- (3) Radiologic detection of wedge-shaped bone defects at the periodontal defect sites;
- (4) The probing depth (PD) of the periodontal defect site was 4-8 mm.

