## **(7) Participant inclusion and exclusion criteria and group assignment method**

**1. Inclusion criteria:** In order to be included in this study, subjects must meet all of the following criteria:

- (1) Subjects must be between the ages of 18 and 65 years old, and there are no gender restrictions for inclusion in this study;
- (2) Subjects must voluntarily participate in this clinical study and sign an "Informed Consent Form";
- (3) Radiographic examination of the periodontal defect site reveals a wedge-shaped bone defect;

- (4) PD at the periodontal defect site ranges from 4 to 8mm.

**2.Exclusion criteria:** Subjects who meet any of the following criteria will be excluded from this study:

- (1) Subjects with hypertension who have blood pressure readings of systolic blood pressure  $\geq 180\text{mmHg}$  or diastolic blood pressure  $\geq 110\text{mmHg}$  within one month prior to the surgery will be excluded from this study;
- (2) Subjects with systemic diseases such as malignancy (including those with positive tumor screening results), diabetes, heart failure due to heart disease, myocardial infarction within the past six months, angina symptoms within the past six months, or congenital heart disease will be excluded from this study;
- (3) Subjects who have used NSAIDs or corticosteroids within three months prior to the surgery, or those who have been on long-term steroid therapy, or have used bisphosphonate medications, will be excluded from this study;
- (4) Systemic infectious patients;
- (5) Patients with periodontal defects and adjacent periodontal tissues that have received surgical treatment;
- (6) Patients with known allergies to any materials that may be used during the surgical procedure (such as patients with allergy prone constitution or history of allergy to blood products);
- (7) Patients with severe periodontitis (alveolar bone resorption exceeding two-thirds of the root length);
- (8) Patients with severe liver or kidney dysfunction;
- (9) Patients with bleeding tendencies or coagulation disorders (patients with  $\text{WBC} < 3.0 \times 10^9/\text{L}$  or  $\text{PLT} < 60 \times 10^9/\text{L}$ );
- (10) Patients infected with HIV or hepatitis B virus;
- (11) Patients who had unprotected sexual activity within one month prior to screening;
- (12) Pregnant or lactating females or females using female hormone contraceptives;

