**In the second phase, there are 3 groups, and the therapeutic dose of stem cell preparation is as follows:**

■ **Normal saline control group:** The therapeutic dose was 0.6 mL/tooth position, and normal saline 0.6 mL/tooth position/person.

■ **Stem cell therapy group:** The therapeutic dose was 0.6 mL/tooth position, the cell volume was about  $1 \times 10^7$  hDP-MSC cells/tooth position/person, and the suspension was Normal saline 0.6 mL.

■ **Stem cell secondary administration group:** The first treatment dose was 0.6 mL/tooth position, and the cell volume was about  $1 \times 10^7$  hDP-MSC cells/tooth position/person. The suspension was 0.6 mL of normal saline. One month later, the second treatment dose was the same as the first treatment dose of 0.6 mL/tooth position, the cell volume was about  $1 \times 10^7$  hDP-MSC cells/tooth position/person, and the suspension was 0.6 mL of normal saline

**3. Stem cell preparation treatment:** local bilateral multi-point injection of a single affected tooth of the subject.

(1) **Treatment operation procedures:** under local anesthesia, use a periodontal probe to determine the position of the alveolar ridge, insert the needle at the bottom of the periodontal pocket (in the tissue around the bottom of the periodontal pocket), and wait for the needle to reach the periodontal ligament on the medial side of the alveolar ridge, and touch the junction between the bone surface and the tooth root, and use 1ml screw. The rotary syringe is injected at multiple intervals on both sides of the buccal (lip) and tongue and palate, and each injection time is 20-30 seconds. The insertion point of the needle is located on the surface of the tooth root to ensure that the injected drug can accumulate at the tooth root. After the end of the treatment with bilateral multi-point local injection of hDP-MSC cells/normal saline, all subjects underwent 2-hour adverse reaction observation and safety evaluation in the periodontology/emergency comprehensive care center.

(2) **Course of treatment:** In the first phase of this study, one local injection administration is a course of treatment. In the second phase of this study, two local injections were administered as a course of treatment, and subjects in the stem cell secondary administration group were administered with one local injection one month after the first dose.

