### (2) Secondary efficacy measures

- **【Radiological detection index】** D90±3, D180±5, D360±5 were examined during the screening period and follow-up period, and the indicators in the screening period were used as the baseline index, and the measured value of D180±5 was used as the evaluation endpoint.
- Change in periodontal defect height at 3 months, 6 months, and 12 months after the end of treatment compared to baseline (CBCT measurements, change in periodontal defect height = difference in distance from enamel bone boundary to alveolar crest).
- Change in mean density of alveolar ridge after 3 months, 6 months, 12 months after the end of treatment compared to baseline (CBCT measurement results).

[Oral clinical testing indicators]: During the screening period, pre-administration, and follow-up periods, D90±3, D180±5, and D360±5 were examined with Florida probes, and the measured values of D90±3 were used as the evaluation endpoints.

- Periodontal probing depth PD compared to baseline
- Periodontal healing compared to baseline (probing bleeding index BOP, gingival recession GR, tooth looseness TM).

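### The CBCT defect-height endpoint is read to the alveolar crest, so as worded it does not register bone fill below a stable crest in the wedge-shaped defects the trial selects

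*Protocol*

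**What the plan says.** The protocol lists two CBCT measures as secondary efficacy endpoints: change in periodontal defect height and change in mean density of the alveolar ridge. Both are compared with screening, and in section (15) "the measured value of D180±5 was used as the evaluation endpoint".

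Height is defined twice, with the same landmarks:
- Section (15), secondary efficacy measures: "change in periodontal defect height = difference in distance from enamel bone boundary to alveolar crest".
- Scenario summary, effectiveness evaluation: "change of periodontal defect height = difference in distance from the cemento-enamel to the top of the alveolar ridge".

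All three inclusion lists (scenario summary, section (V) 2.2, section (7)) require a wedge-shaped defect. Section (7) puts it as "Radiographic examination of the periodontal defect site reveals a wedge-shaped bone defect".

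The injection procedure names two separate places. A probe finds the top of the alveolar ridge. The needle then goes in at the pocket bottom until, in the wording of section (12), it can "touch the junction between the bone surface and the tooth root".

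Section (IV) 3 gives the expected imaging result as two alternatives. One is hard-tissue gain around the injected tooth and at the edge of the alveolar bone. The other is "or the volume of the periodontal hard tissue defect reduced".

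**The concern.** A wedge-shaped (angular) defect normally slopes from the crest down to a base on the root surface, so its vertical extent is set by its base. A measure called defect height that stops at the crest describes the crestal bone level and leaves out the depth of the defect beneath it. If bone forms at the base and the crest does not move, the measure does not move either. If the crest remodels downward during repair, the measure records a worsening.

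This is the only dimensional bone endpoint in the protocol; no defect depth, fill or volume is listed. A null D180 result could be read as no defect repair when the measure could not have shown it. A change confined to the crest could be reported as a change in the defect.

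**Working it through.** The protocol gives no figure to reproduce here: no distances, no expected change and no standard deviation for the CBCT measures. The check is therefore geometric.

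**Notation**
- a = CEJ to crest, b = crest to defect base, so CEJ to base = a + b.
- f = fraction of the wedge filled from its base.
- c = crest change (negative means loss).
- Planned measure: improvement = a before minus a after = c. Neither b nor f enters.
- CEJ to base: improvement = f × b while the base stays below the crest. With complete fill the base meets the crest, so improvement = b + c.

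**Assumed inputs (not in the protocol):** a = 3 mm; b = 2 to 4 mm; f = 50% or 100%; c = 0 or −0.5 mm.

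| Wedge depth b | Fill | Crest change | Planned measure (CEJ to crest) | CEJ to base |
|---|---|---|---|---|
| 2 mm | 50% | 0 | 3 − 3 = 0 mm | 5 − 4 = 1.0 mm gain |
| 4 mm | 50% | 0 | 3 − 3 = 0 mm | 7 − 5 = 2.0 mm gain |
| 2 mm | 100% | 0 | 0 mm | 5 − 3 = 2.0 mm gain |
| 4 mm | 100% | 0 | 0 mm | 7 − 3 = 4.0 mm gain |
| 2 mm | 50% | −0.5 mm | 3 − 3.5 = 0.5 mm worse | 5 − 4 = 1.0 mm gain |
| 4 mm | 50% | −0.5 mm | 0.5 mm worse | 7 − 5 = 2.0 mm gain |
| 2 mm | 100% | −0.5 mm | 0.5 mm worse | 5 − 3.5 = 1.5 mm gain |
| 4 mm | 100% | −0.5 mm | 0.5 mm worse | 7 − 3.5 = 3.5 mm gain |

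The zero in the first four rows does not depend on the assumed sizes: with c = 0 the planned measure is 0 mm for any b and any f. Only the amount missed depends on them.

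**Against the stated expectations.** Gain at the bone edge changes a, so the planned measure captures it. A smaller defect under a stable crest changes b only, so the planned measure misses it.

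**Why both distances are needed.** Crest-to-base depth is the difference between the two distances, and it can shrink because the crest resorbs. In the 4 mm wedge with 50% fill and 0.5 mm crest loss, depth falls from 7 − 3 = 4 mm to 5 − 3.5 = 1.5 mm. Of that 2.5 mm reduction, 2 mm is fill and 0.5 mm is crest loss. Reading both distances separates the two.

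**The case against.** The strongest reply is that the landmark is unclear rather than wrong. The text is a translation, the two definitions name their landmarks in different words, and a measure called periodontal defect height might be meant to be read at the bone edge beside the treated root. If so, fill would register. Nor does the protocol itself say that the defect floor lies below the crest; that comes from the ordinary meaning of a wedge-shaped defect. This reading cannot be excluded. But neither definition states it, the scenario summary's reference to the top of the ridge points the other way, and the injection procedure names the ridge top separately from the bone-root junction. If the bone edge at the root was intended, the wording still needs correcting.

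Other objections stand and limit the point:
- A reader might infer that CBCT cannot show defect fill at all in this trial. The documents do not support that. Mean density is a second CBCT measure and may pick up some fill. With no stated region of interest, this can be neither relied on nor ruled out.
- A reader might infer that a result driven by crest height alone would be spurious. It would not be: gain at the bone edge is one of the expected results.
- Slice matching, reading plane and the density region are commonly settled in an imaging manual or analysis plan, so their absence here is not a fault.
- The measure is secondary, in a study classed as exploratory. Probed attachment level at D90 (primary) and probing depth do not use it.

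**Conclusion.** The point holds for the CBCT defect-height endpoint only. As worded, it responds to crest height and gives 0 mm change for any amount of fill below a stable crest. It can therefore test the bone-edge part of the expected imaging result but not the reduced-defect part. For assumed wedges 2 to 4 mm deep with 50% fill and a stable crest, it misses 1 to 2 mm of gain at the base.

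This rests on two readings: that wedge-shaped has its ordinary meaning, with a floor below the crest, and that crest means the top of the ridge, as the scenario summary says. The millimetre figures illustrate the mechanism and do not estimate what this trial would miss. The documents do not support going further, to a claim that the imaging data are uninformative or that the primary conclusion is at risk. It is a worthwhile, inexpensive correction to a secondary endpoint.

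**What to change.** In the scenario summary (effectiveness evaluation) and section (15), secondary efficacy measures, define change in periodontal defect height as the change in distance from the CEJ to the base of the wedge-shaped defect at the injected tooth. Keep CEJ to crest as a separately named crestal-level measure, so that crest-to-base depth can be derived and fill distinguished from crest change.

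The imaging measurers, who are already blinded, can read both distances from the CBCT scans already scheduled at screening, D90, D180 and D360. The cost is a wording change in two places and one extra distance per scan. Stored scans can be re-measured, and no visit or exposure is added.

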## **(16) Recording requirements for adverse events and reporting methods and treatment measures for serious adverse events**

### **1. Security Data Collection**

The safety of stem cell preparations was assessed by recording, reporting, and analyzing baseline conditions, adverse events, vital signs, laboratory tests, and oral examinations. Throughout the study, any adverse events experienced by the subjects will be comprehensively assessed starting with the subject's signing of informed consent.

Subjects who cannot undergo safety evaluation can be replaced by newly enrolled subjects, such as subjects who have not completed the study according to the requirements of the protocol, including those who have withdrawn early, do not meet the inclusion criteria, and have not completed the treatment and visits as specified in the protocol.

Subjects may withdraw from the study at any time without giving any reason. If the subject has poor compliance or violates the protocol, the investigator can also decide whether to withdraw the subject from the study.

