**2.4 Withdrawal/Discharge Criteria:**

- (1) Subject has experienced adverse event during the course of the study that, in the opinion of the investigator, precludes continuation of the study;
- (2) Subjects have poor compliance and are unable to complete follow-up visits on time;
- (3) Use of other medications that affect tolerability or safety judgment, such as glucocorticoids, bisphosphonates, estrogens;
- (4) Use of other foods that affect tolerability or safety judgment, such as betel nut, or

tough foods that require prolonged chewing, resulting in bite force burden, such as beefsteak;

- (5) Subjects who wish to withdraw from the clinical study and request to investigator;
- (6) Female subjects become pregnant during the study;
- (7) Drop-out.

**2.5 Subgroup design:** The study conducted 2 phases, 96 subjects were recruited.

In phase I, there were 2 groups and 46 subjects were enrolled. After the subjects with a clinical diagnosis of chronic moderate periodontitis signed an informed consent form and met the inclusion criteria while did not meet the exclusion criteria, the investigator randomly assigned them to DPSCs injection group, approximately 23 subjects; saline injection group, approximately 23 subjects, based on the randomization grouping codes provided by the statistician. The randomization envelopes were collected by the Numerical Statistics Unit upon completion of this phase. The investigator selected the proposed treatment sites for the subjects (individual tooth site/subject). All subjects were treated with periodontal basic therapy and perform bilateral multi-point inject hDP-MSC/saline injection immediately after the completion of periodontal basic therapy.

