**4. verification of inclusion and exclusion criteria:** The researchers screen subjects who meet the inclusion criteria and do not meet the exclusion criteria. Comprehensive assessments are conducted for the enrolled subjects to verify if they meet all the screening and inclusion criteria.

**5. allocation of treatment/randomization numbers:** Once the researchers confirm that the subjects meet all the inclusion criteria during the screening period, they will allocate randomization numbers to the subjects based on the randomization codes provided by the statisticians. This random allocation determines the group assignment for each subject. During the baseline/treatment period, the researchers will once again confirm that the subjects meet all the inclusion criteria and inform them of their final group assignment for enrollment.

**6. study compliance management:** Once subjects receive their randomization numbers and are assigned to the researchers involved in this study, it becomes the responsibility of the researchers to track and follow up with the subjects. The researchers should diligently adhere to the study protocol and informed consent form, ensuring that the subjects fully understand the study requirements and cooperate with the research. They should also regularly remind the subjects of scheduled follow-up appointments through phone calls.

**7. compensation and reimbursement:** Subjects participating in this study will receive a fee of 300 RMB per visit as compensation for transportation expenses and loss of income. The researchers are responsible for providing this compensation in cash to the subjects at the end of each visit. If the subjects are able to complete all the scheduled visits for the study, they will receive a total of 7 compensation payments, amounting to 2100 RMB per subject.

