## **(XVIII) Sample case report form (see Annex 2: Case Report Form (CRF))**

## **(XIX) Statistical analysis of study results**

### **1. Data management**

This study used paper version of the original medical record book (see Annex 3: "Original Medical Record Book") for data collection, which was conducted by the researcher in accordance with the GCP and the requirements of the study protocol to fill in the original medical record book accurately, timely, truthful, complete and standardized, signed and dated. The present study used Clinflash EDC (Electronic Data Capture) system, which was used for data collection by the entry personnel according to the original medical records. The data were entered into the EDC in an accurate, timely, complete and standardized manner in accordance with the EDC guidelines. eCRFs were completed by a supervisor assigned by the preparation facility. The completed eCRF will be logged into the EDC by the supervisor assigned by the preparation institution at the research center to check the consistency between the eCRF data and the source data, and any problems found can be challenged online at any time. If problems are found, they can be challenged online at any time. The data administrator will manually check the data, and if there is any problem, he/she will send out a query to the researcher for confirmation and answer the query.

After the data review is completed, the principal investigator, data management personnel, statistical analysts, and the preparation organization will jointly review the data and complete the final definition and judgment of the analyzed population. The database is locked by the data management staff after the electronic signature of the principal investigator is completed.

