## **(XX) Follow up plan and implementation methods**

The follow-up period of this study was 12 months, with telephone follow-up at  $D7 \pm 1$  after local injection treatment and regular follow-up at  $D30 \pm 3$ ,  $D90 \pm 3$ ,  $D180 \pm 5$ , and  $D360 \pm 5$ . The investigator should observe the subjects strictly according to the protocol, and the subjects should try to follow up regularly as requested by the investigator. During the study period, treatment and follow-up should be performed in strict accordance with the protocol, taking into account the fact that a time window of  $\pm 3$  days is allowed from 1 month after treatment with the stem cell preparation, and a time window of  $\pm 5$  days is allowed from 6 months after treatment. If a subject exceeds the window at a follow-up visit, the next follow-up visit should be recalculated based on the time of the previous visit.

The examinations required to be performed at each follow-up visit were conducted by the investigator, and the relevant examinations were conducted in the imaging department, laboratory department and other specialized departments of the research center, and timely, accurate and complete records were made of the clinical indicators, laboratory results and imaging results of each observation, and of the combination of medications, adverse events, and so on. For subjects with adverse reactions, all indicators of the screening period were followed up until they were normalized.

**1. Post-treatment follow-up 1:** Telephone follow-up 1 week ( $D7 \pm 1$  day) after the end of treatment.

- a. Record of adverse events
- b. Record of co-administration of drugs/treatment

**2. Post-treatment follow-up 2:** 1 month ( $D30 \pm 3$  days) after the end of treatment.

a. Vital signs: respiration, heart rate, blood pressure (systolic, diastolic), temperature (axillary), clinical assessment of the general body condition, and another checkup  $2h \pm 30min$  after the end of the second administration of treatment for the subjects in the secondary stem cell administration group in the second phase of this study.

b. Laboratory tests:

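### Open-label investigators may withdraw injected subjects before D90 and replace them, so the primary attachment-level comparison can become one of retained subjects

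*Protocol*

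**What the plan says.** **Replacement.** Section (16), 1. Security Data Collection: "Subjects who cannot undergo safety evaluation can be replaced by newly enrolled subjects, such as subjects who have not completed the study". Later in that sentence the examples are widened: "including those who have withdrawn early, do not meet the inclusion criteria, and have not completed the treatment and visits as specified in the protocol".

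**Withdrawal.** The same section adds: "If the subject has poor compliance or violates the protocol, the investigator can also decide whether to withdraw the subject from the study". The withdrawal criteria appear in the synopsis, in section (V) 2.4 and in section (7) 3. In (V) 2.4 they include "Subjects have poor compliance and are unable to complete follow-up visits on time", and "Use of other foods that affect tolerability or safety judgment, such as betel nut, or" tough foods that need long chewing. Nothing confines them to the time before injection. Section (16) 4, item (4), lets the researcher evaluate withdrawal when periodontitis progresses.

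**Late visits.** Section (XX) treats lateness differently: "If a subject exceeds the window at a follow-up visit, the next follow-up visit should be recalculated" from the previous visit.

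**Blinding and allocation.** Subjects and injecting investigators are unblinded. Periodontal data collectors and image measurers are blinded ((V) 3). The group is determined before D-2 ((V) 4, randomised grouping). On D1 the researchers confirm eligibility again and "inform them of their final group assignment for enrollment" (section (9), item 5).

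**Outcome and analysis.** The probe is used at screening, before injection, and at D90, D180 and D360. AL at D90 is the primary endpoint (section (15) 2). The FAS, which carries the main conclusion, needs use of study drug and at least one efficacy assessment, with LOCF for missing main indicators (section (XIX) 2(1)). The principal investigator, data managers, statistical analysts and the preparation organization "will jointly review the data and complete the final definition and judgment of the analyzed population" (section (XIX) 1). For withdrawn subjects, section (XX) asks for an examination of periodontal health status and a record of the reason and time. It asks for no D90 AL.

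**The concern.** Random allocation protects the comparison only if each subject's D90 result is obtained and counted whatever happens after allocation. Here someone who may know the arm can end a subject's participation after injection on grounds with no objective threshold. One ground, disease progression, is close to the outcome itself. If such decisions differ between arms and relate to how the tooth is doing, the remaining subjects are no longer comparable.

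Replacement then restores the headcount, so the loss is less visible. The rule also does not fall evenly. Only the double-injection arm has a treatment after D1, so only there can a subject miss treatment after D1 and become replaceable on that ground, for instance after a reaction to the first injection. Selective loss needs no bad faith.

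The repeat eligibility check on D1 opens a second route. The group is already determined, those failing inclusion criteria are replaceable, and the FAS counts only subjects who used study drug.

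**Working it through.** **1. What happens to a subject withdrawn, by time**

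- *After D90.* The D90 AL exists and the subject stays in the FAS. Only the PPS requires 6 months of observation.
- *After injection, before D90.* No post-injection probe examination has taken place and none is required. If the FAS needs a post-injection assessment, the subject drops out of it. If the pre-injection D1 examination counts as the assessment, LOCF carries baseline AL forward. Section (15) adds to the doubt by listing D7 and D30 as efficacy evaluation times, although no probing is scheduled then. On every reading the true D90 value is missing.
- *After allocation, before injection.* The subject has used no study drug and is outside the FAS.

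**2. Inputs**

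Section (8) gives a total of 96 with arms of about 33, 33 and 30. This checks: 46/2 + 50/5 = 33 (saline), 46/2 + 50/5 = 33 (single), 50 × 3/5 = 30 (double), sum 96. Alpha is 0.05 and power 0.80. The formula's SD and difference have no values, and no dropout rate is stated. Back-solving the two-group formula gives the detectable standardised difference:

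- 33 v 33: (1.960 + 0.842) × √(2/33) = 0.69
- 33 v 30: (1.960 + 0.842) × √(1/33 + 1/30) = 0.71

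**3. Bias under assumed selective withdrawal**

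Assume no true effect and 33 per arm. A fraction w of one cell arm is withdrawn before D90 on a cue that correlates ρ with a poor D90 result, while saline losses are random. The retained mean shifts in favour of cells by ρ × φ(z) / (1 − w) SD, where z is the 1 − w normal quantile.

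- w = 10%: φ(1.282)/0.90 = 0.1755/0.90 = 0.195. Times 0.3 gives 0.06, times 0.5 gives 0.10.
- w = 20%: φ(0.842)/0.80 = 0.280/0.80 = 0.350. Times 0.3 gives 0.11, times 0.5 gives 0.18.

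A simulation of a single cell-versus-saline comparison (8,000 runs per cell; Monte Carlo SE near 5% is √(0.05 × 0.95/8000) = 0.24 percentage points) agrees:

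| Withdrawn | ρ | Bias, replaced (SD) | Type I error, replaced | Bias, not replaced (SD) | Type I error, not replaced |
|---|---|---|---|---|---|
| 10% | 0 | 0.00 | 4.8% | 0.00 | 4.9% |
| 10% | 0.3 | 0.06 | 5.6% | 0.06 | 5.1% |
| 10% | 0.5 | 0.10 | 6.7% | 0.10 | 6.2% |
| 20% | 0 | 0.01 | 5.0% | 0.00 | 4.9% |
| 20% | 0.3 | 0.11 | 7.2% | 0.11 | 7.0% |
| 20% | 0.5 | 0.18 | 10.9% | 0.18 | 10.0% |

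Against the detectable 0.69 SD, the range is 0.06/0.69 = 9% to 0.18/0.69 = 26%. At ρ = 1, a limiting case, the replaced figures are 0.20 SD and 13% (w = 10%), and 0.35 SD and 35% (w = 20%).

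The bias columns are practically the same with and without replacement. The harm comes from losing the D90 outcome of injected subjects. Replacement restores the number and makes the loss harder to see.

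**The case against.** Much can be said for the plan, and several stronger readings fail.

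- *A reader might infer that the whole trial becomes a completers' comparison.* It does not. Subjects withdrawn after D90 keep their primary value in the FAS, and AL and CBCT measurers are blinded.
- *A reader might infer that safety data are thrown away.* Section (XIX) 2(1) keeps early terminations in the safety analysis, and section (16) 8 follows adverse events to baseline level or final outcome. What may be lost is later scheduled follow-up.
- *A reader might infer that more than 96 would be randomised and only 96 reported.* Replacement is optional, nothing says a replaced subject's data are deleted or unreported, and a description of subject distribution is planned. The protocol is silent on how a replaced subject is analysed and how the new one gets a code.
- *A reader might infer that everyone who settles the analysis sets knows the allocation.* The statistical analysts are stated to be blinded. For the other parties no masking is described.
- *A reader might infer that withdrawal after injection has nothing left to stop.* In the double-injection arm a D30 injection remains, so withdrawal can stop treatment there.
- *Criterion (2) joins poor compliance with inability to attend on time,* so one late visit need not trigger it. That stands, but its relation to the re-timing rule in section (XX) is left open.

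It could also be said that a separate analysis plan may settle the sets. Withdrawal and replacement are conduct rules, though, and no analysis plan can recover a D90 AL that was never measured. The exposure before D90 therefore remains.

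**Conclusion.** The point holds in a limited form. The protocol's own rules allow the D90 AL of an injected subject to be lost at the discretion of someone who may know the arm, allow that subject to be replaced, and define the main efficacy set so that the subject may not count. The primary comparison can therefore become one of retained subjects. Nothing in the protocol shows that it will.

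The size cannot be derived from the protocol. About 0.06–0.18 SD of bias and a type I error of about 5.6–10.9% rest on three assumptions: 10–20% withdrawn before D90 in one arm, a correlation of 0.3–0.5 between the reason and a poor result, and random loss in the other arm. With no correlation there is no bias. The change is worth making because it is mainly one of wording and it protects the primary endpoint.

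**What to change.** 1. **Section (16) 1.** State that replacement never removes a randomised subject. Any added subject takes the next randomisation code, and the original subject stays in the analysis and safety sets.
2. **Sections (V) 2.4, (7) 3, (16) 1, (XX) and the synopsis.** Separate stopping study treatment from leaving follow-up. Ask every injected subject to attend D90 and later visits for AL unless consent is withdrawn. For the analysis, non-compliance, lateness or diet affects only the PPS.
3. **Sections (V) 4, (9) and (XIX) 1.** Complete the eligibility check before the group is revealed, and classify the analysis sets with group codes masked.
4. **Late visits.** Reconcile the withdrawal criteria and section (16) 1 with the re-timing rule in section (XX). The clinical criteria for stopping treatment, including those on concomitant drugs and disease progression, are for the sponsor to settle.

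The cost is protocol wording, the effort of bringing withdrawn subjects back at D90, somewhat noisier FAS data and fewer clean completers. If numbers are a worry, planned recruitment can be raised openly: at an assumed 10% loss, 33/0.90 = 36.7, so 37 per arm. Without that, power at 0.69 SD would fall from 80% to 75.7%.
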